### Population, study setting and sample size

The target population for this study is composed of Canadian PLHIV. According to the Public Health Agency of Canada (PHAC) [30], there were approximately 78,500 PLHIV living in Canada in 2013. Ontario accounted for the highest proportion of new reported PLHIV (39.6 % of reported positive HIV tests), followed by Quebec (21.7 %), and British Columbia (13.0 %). Thus, recruitment for this study will take place mainly in medical clinics and community organizations working with PLHIV in Ontario, Quebec, and British Columbia.

To participate, PLHIV must: 1) be 18 years of age or older; 2) be able to read and understand French or English; and 3) have access to the Internet.

To achieve the study’s objective, 375 participants per group are needed, for a total sample of 750 participants. This sample size was estimated to ensure 80 % statistical power for a 2-tailed chi-square test, at a significance level of α = 0.05, to detect any difference equal to or higher than about 10 % between the failure rates (failure to change the chosen behaviour-binary outcome) estimated in ITT analyses for the two randomization groups. This calculation takes into account the two likely limitations of the study: possible misclassification of self-reported outcomes and attrition. Similar to other online trials (Schubart review’s [31]: 15 trials reported less than 20 % of attrition), we expect up to 20 % attrition during the 6 months of follow-up.

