### Measures/outcomes

All outcomes will be measured with a self-administered online questionnaire hosted on a secured Web page and will be collected at three times: baseline (t_0,_ 46 questions), and three (t_1,_ 26 questions) and 6 months (t_2,_ 34 questions) after baseline. Based on Prochaska’s [32] work on smoking cessation, physical activity and healthy eating, 6 months is the amount of time needed for this sort of health behaviour change to occur.

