#### Randomization

As recommended in the CONSORT-EHEALTH statement, participants will be randomized only after they have completed the baseline assessment [45]. They will be randomly assigned to either control or experimental group with equal probabilities (1:1 allocation ratio). The allocation sequence has been generated by a permuted block randomization list. This method will ensure close balance of the number of participants in each group at any time during the study.

The allocation process (concealment and implementation) will be entirely computerized. The sequence will be programmed into the database intervention and the participants will be informed automatically by email about the group to which they are assigned.

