### Analysis

Descriptive statistics will be used to compare the participants in the two groups with means, medians, standard deviations, and inter-quartile ranges for continuous and frequency distributions for categorical and binary variables. Any variable for which the difference between the two arms is considered clinically important will be adjusted through multivariable analyses. The principal analyses will focus on testing the hypothesized differences between the two trial groups using the Intention-to-Treat (ITT) analysis.

The primary outcome of the success/failure in the adoption of the chosen health behaviour at 6 months will be analyzed as a binary outcome. Accordingly, the primary hypothesis will be tested with the 2-tailed chi-square test, with 1 degree-of-freedom (df), at α = 0.05 significance level. Next, to adjust the intervention effect for potential confounders, we will build a multivariable logistic regression with adjustment for any baseline characteristics for which the descriptive analyses indicate a clinically important difference between the two groups. The multivariable model will also adjust for baseline values of the chosen health behaviour. In the multivariable logistic regression, the effect of the intervention will be estimated by the adjusted Odds Ratio, with 95 % CI, and its statistical significance will be tested by the model-based 1-df Wald chi-square test at 2-tailed α = 0.05. During ITT analyses, all participants will be assessed in their respective randomization group as to whether they are following the procedure or have been lost to attrition during the follow-up. In this manner, all participants lost to follow-up before 6 months will be assigned a ‘failure’, regardless of the group to which they were assigned randomly. This approach is conservative because it reduces the estimated difference between the two randomization groups.

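### Counting all dropouts as failures is called conservative without condition, but the rule can enlarge or create a difference when control attrition is materially higher

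*Protocol article*

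**What the plan says.** The Analysis section sets the rule for the 6-month composite success/failure outcome: "all participants lost to follow-up before 6 months will be assigned a" failure code, whichever arm they were in. It then justifies the rule: "This approach is conservative because it reduces the estimated difference between the two randomization groups". The section states no condition on attrition by arm.

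The rule feeds the single primary comparison: "the primary hypothesis will be tested with the 2-tailed chi-square test", with 1 degree of freedom at the 5% level. The sample size section gives one overall attrition figure, up to 20% over 6 months. It does not split this by arm or say that the arms are expected to be equal. The outcome depends wholly on participants returning a form: "All outcomes will be measured with a self-administered online questionnaire hosted on a secured Web page". According to the Abstract and the Measures/outcomes section, this happens at baseline, 3 months and 6 months.

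**The concern.** Under this rule each arm's analysed success rate is the success rate among completers multiplied by the proportion retained. The comparison therefore mixes behaviour change with retention. At 20% attrition, 150 of 750 primary outcomes would be assigned rather than observed, so the direction of any imbalance matters.

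The documents make unequal attrition possible, though they do not predict it. One arm receives three to seven tailored sessions hosted by a virtual nurse, and the other a list of five websites. The Blinding section says that participants know which intervention they received. If control participants leave in materially larger numbers, part of an apparent benefit could be retention, and the word conservative would stand in the published protocol as a ready defence of it.

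**Working it through.** **Inputs from the article.** 375 per arm, 1:1 allocation, two-sided chi-square test at 5%, 80% power, a difference of about 10 points in ITT failure rates, attrition up to 20% overall. The base rate and the attrition by arm are not given, so the values below are assumptions.

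**The plan's own figure.** With the pooled formula n = [1.96·√(2·p̄·(1−p̄)) + 0.8416·√(p₁(1−p₁)+p₂(1−p₂))]² / d² and failure rates of 65% and 55%:

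- 1.96·√0.48 = 1.358 and 0.8416·√0.475 = 0.580
- (1.938)² / 0.01 ≈ 376 per arm, which agrees with the stated 375

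At the least favourable base rate (55% against 45%), 375 per arm still gives 78.3% power. The sample size is not in question.

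**What the rule does to the difference.** For each arm let r be success among completers, q the true success among dropouts and a the attrition (E experimental, C control).

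- Full-data difference: [(1−a_E)r_E + a_E·q_E] − [(1−a_C)r_C + a_C·q_C]
- Difference under the rule: (1−a_E)r_E − (1−a_C)r_C
- Rule minus full data: a_C·q_C − a_E·q_E

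The rule lowers the difference when a_E·q_E exceeds a_C·q_C, leaves it unchanged when they are equal, and raises it when a_C·q_C is larger.

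**Numbers.** Take q = r in each arm and n = 375 per arm. The rejection probability comes from the pooled z test. For the second row: rates 0.40×0.85 = 0.34 and 0.40×0.75 = 0.30; critical difference 1.96·√(2×0.32×0.68/375) = 0.0668; standard error √((0.34×0.66+0.30×0.70)/375) = 0.0340. Then z = (0.04−0.0668)/0.0340 = −0.79, which gives 21.6% in favour of the experimental arm and 21.7% in both tails.

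| True success E / C | Attrition E / C | Analysed E / C | Difference (points) | Rejection |
|---|---|---|---|---|
| 40 / 40 | 20 / 20 | 32.0 / 32.0 | 0 | 5.0% |
| 40 / 40 | 15 / 25 | 34.0 / 30.0 | +4.0 | 21.7% |
| 50 / 40 | 20 / 20 | 40.0 / 32.0 | +8.0 | 62.7% |
| 50 / 40 | 15 / 25 | 42.5 / 30.0 | +12.5 | 94.7% |
| 50 / 40 | 18 / 22 | 41.0 / 31.2 | +9.8 | not computed |
| 50 / 40 | 25 / 15 | 37.5 / 34.0 | +3.5 | 16.8% |
| 50 / 40 | 30 / 10 | 35.0 / 36.0 | −1.0 | 1.2% |

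Rejection counts both tails in the no-effect rows and favours the experimental arm in the others. With no effect and a 15/25 split, it runs from 16% at 30% success to 38% at 60%. A milder 17.5/22.5 split at 40% success gives about 9%. Simulations of 200,000 trials for several such settings agree with the formula to within half a point.

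**Equal attrition is not a full guarantee.** With 20% lost in both arms, completers at 50% and 40%, and dropouts at 20% and 40%, the full-data difference is (0.40+0.04)−(0.32+0.08) = 4 points. The rule reports 0.40−0.32 = 8.

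**The case against.** The strongest defence is that the sentence is right in the cases its authors probably had in mind. Equal attrition shrinks 10 points to 8. Higher experimental attrition shrinks it further, so the 3.5-point case bears out the claimed reduction and does not contradict it. This stands: a reader might infer that the claim holds only under equal attrition, and that is too strong.

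Nor does every excess of control attrition inflate a real effect. At 50% against 40%, with dropouts succeeding at the completers' rate, control attrition must exceed 1.25 times experimental attrition. The 18/22 split still gives 9.8 points, below 10.

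It is also fair that 34% against 30% is a false benefit only if dropouts succeed about as often as completers. If every dropout truly failed, that is the real contrast. But then the rule leaves the full-data difference unchanged and does not reduce it, so the unconditional sentence is not rescued.

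The case for unequal attrition is open in direction. Session burden could drive out more experimental participants. The article describes measurement reminders and gift certificates without distinction by arm, and says participants may not easily tell which group is experimental.

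Two further inferences are not supported. One is that the plan lacks sensitivity analyses: a condensed article may leave these to an analysis plan that is not shown. The other is that failure coding is illegitimate for physical activity and diet: the article defines failure as not having changed the chosen behaviour, and treating non-responders as unchanged matches its baseline-value rule for the cognition scores.

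**Conclusion.** The concern holds as an error in the stated justification. The rule is not conservative in general; its effect depends on which arm loses more successes. With an assumed 15/25 split it turns no effect into 4 points with about 22% rejection, and 10 points into 12.5. With 25/15 it reduces 10 points to 3.5 with 17% power, which is in the direction the article claims but hides a real effect.

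These sizes rest on assumed success rates, assumed attrition by arm, and dropouts succeeding at the completers' rate. A reader might infer that the trial's type I error is 22%, or that the failure rule must be abandoned. The documents support neither, since they give no attrition by arm and the rule remains a permissible primary choice. What cannot stand is the unconditional claim, because it would lend a positive result a strength that the rule does not guarantee.

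**What to change.** Delete the sentence, or limit it to the case where attrition is not higher in the control arm, adding that this presumes experimental dropouts succeed at least as often as control dropouts.

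Missing = failure may stay as the primary rule. Pair it with one or both of:

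- a tipping-point analysis that varies dropout success separately by arm;
- multiple imputation by arm and chosen behaviour, using the baseline and 3-month data already collected.

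Do not describe a positive result as conservative if control attrition turns out to be higher.

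The cost is a wording change, modest programming and an explicit imputation assumption. Imputation under missing-at-random is itself untestable and would overstate success if dropouts mostly failed, which is a reason to use it as a check and not necessarily as a replacement. No new data and no change to the sample size are needed.

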### Study objective and hypotheses

This study aims to evaluate the effectiveness of a Web-based tailored intervention, *TAVIE en santé*, in supporting PLHIV to adopt health promoting behaviours, such as smoking cessation, being physically active and eating healthy.

The primary hypothesis is that at the 6-month follow-up, a significantly higher proportion of experimental group (EG) participants will have succeeded in changing the specific health behaviour that they individually selected (smoking cessation being physically active or healthy eating) when compared with the control group (CG) participants. The secondary hypothesis is that at the 3-month follow-up, compared with CG participants, EG participants will show significantly higher scores on intention, attitude, and perceived control regarding the adoption of their chosen health behaviour.

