#### Secondary outcomes measures: cognitions

*Intention*, *perceived behavioural control*, and *attitude* regarding the adoption of the chosen health behaviours will be measured, respectively, through 3, 3, and 5 items respectively on a 5-point bipolar scale, as recommended by Ajzen and Fishbein [41, 42]. All items reports to the future (“over the next 3 months”) and to the chosen health behaviour (a: stop smoking, b: do more physical activity, c: make better choices regarding fat in my diet). *Intention* is assessed by three items: “I intend to (a, b or c)”; 2) “I will (a, b or c)” and 3) “the chances that I will (a, b or c) are…”. *Perceived behavioural control* is assessed by three items: 1) “I feel that I will be able to (a, b or c)”; 2) “I am confident that I will succeed in (a, b or c)”; 3) “How much control do you have over (a, b or c)?” *Attitude* is measured by asking participants to respond–using five 5-point adjective pairs (unpleaseant/pleasant, useless/useful, bad/good, unsatisfying/satisfying, boring/interesting)–to the statement linked to their chosen behaviour “Smoking cessation would be for me…” or “Doing more physical activity would be for me…” or “Making better choices regarding fat in my diet would be for me…”.

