The secondary outcomes of intention, perceived behavioural control, and attitude, will be evaluated at the 3-months follow-up, and analysed as continuous variables. Thus, the same analytical methods will be used for all these outcomes. The distribution of the outcome scores will be assessed for normality of residuals using the Shapiro-Wilk test. We will assign the individual baseline score for a given outcome to participants who fail to provide data for a given outcome. To test the statistical significance of the un-adjusted difference between the mean values of a given (possibly transformed) outcome observed in the two trial arms at 3 months, we will use the 2-tailed independent-groups student’s *t*-test at α = 0.01. Multivariable linear regression will be used to adjust the estimation and testing of the intervention effect for potential confounders, for which the descriptive analyses indicate a clinically important difference between the two groups. In multivariable linear regression, the effect of the intervention will be estimated by the adjusted mean difference, with 95 % CI, and its statistical significance will be tested by the model-based F-test with 1-df in the numerator, at 2-tailed (Bonferoni-corrected) α = 0.01.

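### Replacing missing 3-month cognition scores with baseline scores shrinks the secondary effects if dropouts would have shared them, and can bias them if scores drift and loss differs by arm

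*Protocol article*

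**What the plan says.** The secondary hypothesis (Study objective and hypotheses) is that at 3 months "EG participants will show significantly higher scores on intention, attitude, and perceived control regarding the adoption of their chosen health behaviour". The Analysis section says that these outcomes "will be evaluated at the 3-months follow-up, and analysed as continuous variables". For missing data it gives one rule: "We will assign the individual baseline score for a given outcome to participants who fail to provide data for a given outcome". For the unadjusted comparison, "we will use the 2-tailed independent-groups student’s *t*-test at α = 0.01". In the regression, "the effect of the intervention will be estimated by the adjusted mean difference, with 95 % CI", and covariates enter where the arms show a clinically important imbalance. The scores "will be measured, respectively, through 3, 3, and 5 items respectively on a 5-point bipolar scale" (Secondary outcomes measures: cognitions), and the items ask about the coming three months.

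On attrition, the sample size section says "we expect up to 20 % attrition during the 6 months of follow-up". It gives no 3-month figure and no split by arm. The Analysis section calls a missing-data rule conservative only for the primary outcome, where missing counts as failure.

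**The concern.** The rule is single imputation by baseline carried forward. It sets every non-responder's change to exactly zero, and the article gives no reason why that should hold.

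It fits these outcomes poorly in two ways. First, because the items look three months ahead, a baseline answer concerns months 0 to 3 and a 3-month answer concerns months 3 to 6. The substituted value therefore answers a question about a different period. Second, a participant who misses only the 3-month questionnaire may still supply a 6-month score, and the rule ignores it.

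Three things are at stake: an effect estimate pulled towards zero, a possible bias of either sign, and standard errors that count substituted values as observed ones.

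**Working it through.** **Inputs from the article.** "375 participants per group are needed, for a total sample of 750 participants"; two-sided alpha 0.01 for these outcomes; attrition up to 20% over 6 months.

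**Assumed, because the article does not give them.** True effect δ; common change from baseline to 3 months (drift); share missing in the experimental and control arms, qE and qC; baseline-to-3-month correlation ρ of 0.5 to 0.6; dropout unrelated to scores within arm. All scores are in SD units.

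**The plan's own figure.** The article states no power for the cognition scores. The 375 per arm belongs to the primary binary outcome. It fits the stated inputs (for example, 376 per arm for failure rates of 65% and 55%), and nothing below depends on how it was reached.

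**Expected estimate.** Take the baseline mean as zero in both arms.
- Experimental arm: (1 − qE)(drift + δ) + qE × 0
- Control arm: (1 − qC) × drift
- Difference: (1 − qE)δ − (qE − qC) × drift

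**Dilution: qE = qC = 0.20, no drift, δ = 0.25.**
- Estimate: 0.80 × 0.25 = 0.20.
- Baseline substitution, t-test: SE = √(2/375) = 0.073; 0.20/0.073 = 2.74; 2.74 − 2.576 = 0.16; power about 57% (simulations gave 55% to 58%).
- Observed scores, 300 per arm, t-test: SE = √(2/300) = 0.0816; 0.25/0.0816 = 3.06; 3.06 − 2.576 = 0.49; power about 69%.
- Observed scores, baseline-adjusted: SE = 0.0816 × √(1 − ρ²), which is 0.0707 at ρ = 0.5 and 0.0653 at ρ = 0.6. Power is about 84% (simulated) and 89%.

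Part of the gain from 57% to 84-89% comes from adjusting for baseline, not from dropping the substitution. Like for like, at ρ = 0.5, the simulated power of a baseline-adjusted regression is about 81% with substituted data and about 84% with observed scores. The first still estimates 0.20, the second 0.25.

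**Other effect sizes** (t-test power, 20% missing per arm):

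| δ | No missing data | Observed only | Baseline substituted |
|---|---|---|---|
| 0.14 | 25.5% | 19.5% | 14.9% |
| 0.20 | 56.5% | 45.0% | 35.0% |
| 0.25 | 80.2% | 68.7% | 56.5% |
| 0.30 | 93.7% | 86.4% | 76.1% |

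**Bias: δ = 0, qE = 0.25, qC = 0.15** (average 20%, the plan's ceiling).
- Drift −0.3: −(0.10)(−0.3) = +0.03. With SE about 0.0736, the rejection rate is about 1.5% to 1.8%.
- Drift −0.5: −(0.10)(−0.5) = +0.05. With SE about 0.0744, the rejection rate is about 3%.
- Drift +0.3 or +0.5: the same sizes with a negative sign.
- Smaller gap, 22% against 18%, drift −0.3: 0.04 × 0.3 = +0.012; rejection rate about 1%.
- Equal loss with drift, or unequal loss without drift: bias 0.00; rejection rate about 1%.

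In the same settings the baseline-adjusted analysis of observed scores gave estimates of 0.00 and rejection rates of about 1%.

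**Precision** (20% missing per arm, ρ = 0.5). The SE with substitution is 0.073 against 0.082 on observed scores for the t-test, and 0.059 against 0.071 for the baseline-adjusted model. Intervals are therefore about 10% to 17% narrower than the collected 3-month information supports.

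**The case against.** The best defence is that the rule may match a sensible target. If people who leave a web programme gain nothing from it and return to where they began, setting their change to zero is right, and 0.20 SD is the correct answer, not a diluted one. With equal loss the rule leans against the intervention, in line with the primary outcome's missing-as-failure rule. This stands as a possibility. But the article neither states nor justifies that assumption for the cognition scores, and its remark about conservatism is confined to the primary outcome.

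Four further points stand and limit the concern.
- Drift and loss by arm are not given anywhere. One might suppose that scores peak at enrolment, but the intervention description provides profiles for people who enter with low attitude or low perceived control, so high entry scores cannot be presumed. Unequal loss is plausible, because participants know their intervention and one arm receives a multi-session programme while the other receives a list of websites. It is not documented.
- A reader might infer that p-values and intervals are wrong whenever scores drift or the arms lose different numbers. They are not: bias under no effect needs both together.
- The standard error is valid for the estimator computed on substituted data. It is too small only as a measure of what is known about the actual 3-month difference.
- A reader might infer that no sensitivity analysis is planned. A condensed article cannot show that. Only the choice of main method is open to criticism.

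**Conclusion.** The concern holds as a modest methods point on the secondary outcomes. Baseline substitution is a poor main analysis for the 3-month cognition scores. If dropouts would have shared the completers' effect, loss at the plan's 6-month ceiling removes a fifth of it (0.25 to 0.20 SD) and leaves the t-test with about 55-57% power at alpha 0.01. If common drift and unequal loss occur together, the estimate under no effect moves by about 0.03 to 0.05 SD in the 25%/15% case, and the false-positive rate is about 1.5% to 3% instead of 1%. Falling scores with more loss in the experimental arm favour that arm; rising scores reverse the sign. The article therefore does not support a claim that the rule favours the intervention, nor a claim that it is reliably conservative.

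These sizes rest on assumed drift, loss by arm, correlation and effect. If loss at 3 months is lower, they shrink in proportion. The primary 6-month analysis is not touched.

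**What to change.** Make the main analysis of each cognition score one of the following, tested at the plan's alpha of 0.01:
- a baseline-adjusted likelihood model of the baseline, 3-month and 6-month scores, with the 3-month difference between arms as its target; or
- multiple imputation by arm under a missing-at-random assumption, using the baseline score, the 6-month score and the chosen behaviour.

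State which effect is being estimated for participants who stop responding. Keep baseline substitution as a sensitivity analysis and, if wanted, add imputation with shifts that differ by arm. Report 3-month loss by arm beside the results.

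The cost is a change of analysis wording, routine software and slightly more analysis work. All the data are already due at the three planned questionnaires. The main analysis would then rely on missing at random, which cannot be verified; the sensitivity analyses probe it.

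Suggested wording: *Each 3-month cognition score will be compared between arms with a likelihood-based longitudinal model adjusted for the baseline score, using all observed scores at baseline, 3 and 6 months. Substitution of the baseline score for missing values will be a sensitivity analysis.*

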### Interventions

During an individualized targeted online assessment, participants will have to choose a health behavior they wish to adopt (smoking cessation or increasing physical activity or adopting healthy eating). This assessment will also determine the participant’s level of intention, perceived behavioural control, and attitude towards to the adoption of the chosen behaviour.

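### Each 3-month cognition score is adjusted for its own baseline only if that baseline happens to look imbalanced, which costs power on the secondary hypothesis

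*Protocol article*

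**What the plan says.** The protocol article's secondary hypothesis is that intention, attitude and perceived control are higher in the experimental arm at 3 months. Under Analysis, these scores "will be evaluated at the 3-months follow-up, and analysed as continuous variables". Four steps follow.

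- **Normality check.** "The distribution of the outcome scores will be assessed for normality of residuals using the Shapiro-Wilk test".
- **Missing scores.** A participant without a 3-month score is given their baseline score.
- **First test.** A two-sided t-test is used: "To test the statistical significance of the un-adjusted difference between the mean values of a given (possibly transformed) outcome observed in the two trial arms".
- **Regression.** A linear model is fitted to "adjust the estimation and testing of the intervention effect for potential confounders, for which the descriptive analyses indicate a clinically important difference", tested "at 2-tailed (Bonferoni-corrected) α = 0.01".

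For the primary binary outcome, the same section plans an unadjusted chi-square test and then a logistic regression with the same imbalance rule, but adds: "The multivariable model will also adjust for baseline values of the chosen health behaviour". The secondary regression has no such sentence.

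On availability, the Interventions section says of the baseline assessment: "This assessment will also determine the participant’s level of intention, perceived behavioural control, and attitude towards to the adoption of the chosen behaviour". The sections on online data collection and on randomization both state that allocation follows completion of the baseline questionnaire.

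**The concern.** When a continuous score is measured in the same way before and after treatment, its baseline value is usually a strong predictor of the follow-up value. Conditioning on it removes outcome variance that has nothing to do with the intervention. The plan uses the baseline score to fill in missing values but does not name it as a covariate. It would enter the regression only through a judgement, made after the baseline data are seen, that the arms differ importantly on it. Two consequences follow: the tests give up precision that costs nothing to obtain, and the content of the adjusted model depends on the data. These tests carry the secondary hypothesis and bear on the determinants that the intervention is designed to change.

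The normality check raises a smaller worry of the same kind, because it leaves the outcome scale open until the data are in.

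**Working it through.** **Inputs from the protocol.** 375 per arm with 1:1 allocation (Population, study setting and sample size); two-sided alpha 0.01 per cognition (Analysis); 3, 3 and 5 five-point items for intention, perceived control and attitude (Secondary outcomes measures).

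**Assumptions.** The standardized effect d, the correlation r between baseline and 3 months, and the proportion of scores missing at 3 months are not given. The protocol expects up to 20% attrition over 6 months; 20% is used here for 3 months.

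**The plan's own figure.** The 375 per arm is for the primary outcome: 80% power, two-sided alpha 0.05, a difference of about 10 points. Failure rates of 65% and 55% give 376 per arm, so it reproduces under that choice; the control rate is not stated. No power is stated for the cognitions, so there is no secondary figure to reproduce.

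**Step 1, unadjusted test.** With SD = 1, SE = sqrt(2/375) = 0.0730. At d = 0.20, d/SE = 2.739, and power = Φ(2.739 − 2.576) = 0.565. The effect detectable with 80% power is (2.576 + 0.842) × 0.0730 = 0.25 SD.

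**Step 2, adjusted for baseline.** The SE is multiplied by sqrt(1 − r²), and the adjusted analysis is worth 375/(1 − r²) per arm analysed without adjustment.

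| r | Variance removed | Power, d = 0.20 | Power, d = 0.25 | Detectable d at 80% | Equivalent n per arm |
|---|---|---|---|---|---|
| unadjusted | 0% | 0.565 | 0.802 | 0.250 | 375 |
| 0.3 | 9% | 0.616 | 0.844 | 0.238 | 412 |
| 0.5 | 25% | 0.721 | 0.916 | 0.216 | 500 |
| 0.7 | 49% | 0.896 | 0.987 | 0.178 | 735 |

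**Step 3, with the plan's carry-forward rule.** If 20% of 3-month scores are replaced by baseline at random and variances are equal at the two times, the mean effect shrinks to 0.8d and the correlation becomes 0.2 + 0.8r. So r = 0.3, 0.5 and 0.7 among completers becomes 0.44, 0.60 and 0.76. At d = 0.20 in completers the effect is 0.16, and Φ(0.16/0.0730 − 2.576) = 0.350 unadjusted. Adjusted power is 0.446, 0.565 and 0.787 by formula, and 0.443, 0.568 and 0.778 by simulation.

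**Step 4, validity.** In simulations of 4,000 trials per setting with no effect, both tests rejected in 0.9% to 1.3% of trials, with and without carry-forward. This is consistent with the nominal 1%.

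**Step 5, Shapiro-Wilk.** Means of 3 or 5 five-point items were simulated at n = 750 with arm-centred residuals, varying item number, mean level and inter-item correlation over 18 scenarios. The test rejected in 98.5% of samples in one scenario and in 100% in the other 17.

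**The case against.** The strongest reply is that this is a matter of efficiency, not error. The unadjusted t-test is valid, only secondary outcomes are involved, and the protocol claims no power for them. That stands, and it limits the weight of the point. It does not remove it, because the covariate is already collected and the section fixes a rule that leaves it out unless it is imbalanced. This is not detail left to an analysis plan.

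A second reply is that the size of the loss is assumed. That also stands: at r = 0.3 the gain at d = 0.20 is only about 5 points, and at r = 0 there is none. However, carrying baseline forward itself makes the analysed correlation positive. Part of that correlation then comes from the imputation, since outcome and covariate are identical for those participants. Step 3 describes the analysis as planned and is no endorsement of the imputation rule.

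Some stronger readings are tempting but are not supported:

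- **That the primary outcome is always baseline-adjusted.** Its first test is an unadjusted chi-square; only its multivariable model includes baseline behaviour.
- **That baseline scores are complete because they drive the tailoring.** Tailoring applies only to the experimental arm. The sound reason is that randomization follows the completed questionnaire.
- **That d = 0.14, quoted in the Background for chronically ill patients, sizes the loss.** It is reported for health behaviours, not for cognitions.
- **That a failed normality test forces a transformation.** The text says only that the outcome may be transformed and gives no trigger. The team is also to be blinded during analysis, which limits steering of the scale towards an arm.
- **That log or square-root transformations would be undefined.** That needs negative item coding, which the protocol does not specify.

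**Conclusion.** The point holds as a loss of power and prespecification on the secondary hypothesis. It is not a validity problem, and the primary analysis is untouched. The inconsistency is narrow: the primary regression prespecifies its baseline value and the secondary regression does not.

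At d = 0.20 and alpha 0.01, the loss runs from about 5 points of power (r = 0.3) to about 33 (r = 0.7) with complete data. With 20% carried forward it runs from about 9 to about 43 points. The direction is secure for any positive r. The size rests on assumed values of r, d and missingness, and the random carry-forward in Step 3 is a further simplification.

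The Shapiro-Wilk step is a minor companion point. At n = 750 it will almost always reject for scores of this kind, so it says little about whether a transformation is needed.

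**What to change.** For each cognition, name as the main test a linear model of the 3-month score on arm and that outcome's own baseline score, fitted whatever imbalance is observed. Keep the unadjusted mean difference as description. Prespecify the untransformed scale, on which the model is robust with 375 per arm, and drop the Shapiro-Wilk test as a guide to transformation.

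State how carried-forward scores are treated in this model, since outcome and covariate coincide for those participants.

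The cost is a change of wording in the Analysis section. No new data, visits or participants are needed.
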